### The secondary outcome

The secondary outcome measure is the accuracy of lesion detection through MRE confirmed by colonoscopy over a 5-point scale (lesions locating at the terminal ileum, ileocecal junction, hepatic flexure of colon, splenic flexure of colon, and rectosigmoid colon, consistency of lesion detection from each bowel segment scoring 1 point, otherwise not scoring). A higher score of distention grade of bowel segments and accuracy of lesion detection represents a better efficacy of bowel preparation for MRE.

### Sample size calculation

The principal analysis will consist of the comparison between the proportions of bowel preparation that have reached physician–patient satisfaction score (degree of discomfort score ≤ 10, out of 50; grade of bowel distention score ≥ 20, out of 25; lesions detection point ≥ 4, out of 5) through mid-gut tubing and taking contrast compounds orally. Group sample sizes of 48 in the tubing group and 48 in the oral group achieve 80% power to detect a difference between the group proportions of 0.2500. The proportion in the tubing group is assumed to be 0.6000 under the null hypothesis and 0.8500 under the alternative hypothesis. The proportion in the oral group is 0.6000. The test statistic used is the two-sided Z test with unpooled variance. The significance level of the test was targeted at 0.0500. The significance level actually achieved by this design is 0.0506.

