### The primary outcome

The primary outcome measures are: (1) degree of discomfort before/during/after bowel preparation for MRE using a visual 5-grade scale (1 = few, 5 = very severe). The bowel preparation includes two procedures, bowel cleaning and bowel distention, during which we use a visual 5-grade scale to describe the severity of nausea, vomiting, bloating, and abdominal pain (1 = few, 5 = very severe), respectively [20]. After the MRE, we use a visual 5-grade scale to describe the severity of abdominal pain and diarrhea. A lower score of adverse symptoms means a better compliance of the patient for bowel preparation for MRE; (2) grade of bowel distention evaluated by a 5-grade scale (1 = 0–20% segmental distention, 2 = 20–40% distention, 3 = 40–60% distention, 4 = 60–80% distention, 5 = 80–100% distention) [17, 21–23]. The distention grades of bowel segments, including jejunum, proximal ileum, distal ileum, right part colon, and left part colon, are assessed by two experienced radiologists, both of whom will be blinded to the information of allocation along above 5-grade scale. Different grades of bowel distention in the MR images achieved through two different methods are shown in the Fig. 4.

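### The discomfort cut-off in the primary success rule equals the lowest score the scale allows, so a patient passes only with the lowest grade on all ten items

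*Protocol article*

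**What the plan says.** **The rule.** The section on sample size calculation of the Protocol article defines success by three conditions: "degree of discomfort score ≤ 10, out of 50", and "grade of bowel distention score ≥ 20, out of 25; lesions detection point ≥ 4, out of 5". The statistical analysis plan section makes the chi-square comparison of the proportions meeting this rule the primary analysis. The sample size rests on the same proportions: "The proportion in the oral group is 0.6000", against 0.85 with tubing, with 48 patients per group for 80% power.

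**The score.** The section on the primary outcome describes "degree of discomfort before/during/after bowel preparation for MRE using a visual 5-grade scale (1 = few, 5 = very severe"). It says that "The bowel preparation includes two procedures, bowel cleaning and bowel distention", during which patients rate the "severity of nausea, vomiting, bloating, and abdominal pain (1 = few, 5 = very severe), respectively". It adds: "After the MRE, we use a visual 5-grade scale to describe the severity of abdominal pain and diarrhea". Table 1 marks the same assessments (four symptoms at each of two time points, then two afterwards) and lists mental pressure as a separate variable.

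**The concern.** The cut-off is written as a tolerance, as if some discomfort were acceptable. On a total built from items that start at 1, the number 10 is the floor and leaves no tolerance. The other two conditions do leave room below a perfect result.

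This threshold decides success in the primary analysis and carries the sample size. If it is stricter than intended, the trial answers a different question from the one planned, and the planning proportions may belong to a different rule from the one written down.

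**Working it through.** **1. The plan's own sample size.** Inputs from the sample size section: 0.60 and 0.85, two-sided alpha 0.05, unpooled variance.
- Variance term: 0.60 × 0.40 + 0.85 × 0.15 = 0.3675.
- n per group = 0.3675 × (1.960 + 0.842)² / 0.25² = 46.2, so 47. Power at 48 is 81.5%.
- Exact power of the planned chi-square test (no continuity correction) at 48 per group is 80.4%.

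The stated 48 per group and 80% follow from the stated rates. What is in doubt is whether those rates belong to the stated rule.

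**2. Number of items.** Nausea, vomiting, bloating and abdominal pain in two procedures: 2 × 4 = 8. Abdominal pain and diarrhea after the MRE: 2. Total: 10. The stated maximum confirms this: 10 × 5 = 50. Adding mental pressure would give 55.

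**3. Attainable range.** Minimum 10 × 1 = 10, maximum 10 × 5 = 50. Of the 5^10 = 9,765,625 possible answer patterns, exactly one has a total of 10 or less: grade 1 throughout.

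**4. The three cut-offs on their attainable ranges.**

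| Component | Range | Cut-off | Position on the range |
|---|---|---|---|
| Discomfort (low is good) | 10–50 | ≤ 10 | (10 − 10)/40 = 0%, the best possible score |
| Distention (high is good) | 5–25 | ≥ 20 | (20 − 5)/20 = 75% |
| Lesion detection (high is good) | 0–5 | ≥ 4 | 4/5 = 80% |

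**5. What the planning rates would require.** Let q be the probability of grade 1 on one item. This is an assumption, since the article gives no item-level data. With independent items, the discomfort part is passed with probability q^10. The correlated figures use a Gaussian latent variable with correlation 0.5 between items.

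| | Independent | Correlation 0.5 |
|---|---|---|
| Pass rate if q = 0.80 | 0.80^10 = 11% | 38% |
| Pass rate if q = 0.90 | 0.90^10 = 35% | 60% |
| q needed for a 60% pass rate | 0.60^(1/10) = 0.950 | 0.90 |
| q needed for an 85% pass rate | 0.85^(1/10) = 0.984 | 0.97 |

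These figures cover the discomfort part alone, before the distention and lesion conditions take their share.

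**6. Power if the true success rates differ.** Exact chi-square power, 48 per arm; the pairs of rates are illustrative.

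| Oral vs tubing | Power |
|---|---|
| 60% vs 85% (planned) | 80% |
| 5% vs 15% | 41% |
| 10% vs 25% | 51% |
| 10% vs 35% | 86% |
| 5% vs 30% | 94% |

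Power falls when the difference shrinks. It rises when the planned difference of 0.25 persists at low rates.

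**The case against.** The strongest defense is that a strict rule is not an impossible one. Grade 1 is labeled *few*, not *none*, so a patient with slight symptoms can be graded 1 on every item and pass. That stands. A reader might infer that the rule fails anyone with any symptom at all, and the stated anchors do not support that.

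A reader might also infer that 0.60 and 0.85 cannot be true under this rule. The documents do not show this. The Background says that some patients may not tolerate a large oral load, but gives no frequency or grade. The Discussion reports pilot symptoms relieved or gone with tubing. What can be said is that the rates have no stated basis under a floor cut-off.

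Nor do the documents show that power must be low, as the last table makes clear, or that the distention and lesion conditions cease to matter, since nothing is given about how the three components behave jointly. That the cut was set as a share of the maximum (10/50 beside 20/25 and 4/5) is a plausible guess about its origin, no more.

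Finally, the damage is contained. Symptom severity and distention are also compared on their full scales by the Wilcoxon test, and those comparisons do not use the cut-off.

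None of this removes the central point. No wording allows a zero grade. A 0–5 scale would reach 50 but has six grades, and a 0–4 scale would reach only 40.

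**Conclusion.** The point holds as a mismatch between a stated cut-off and a stated scale. In the primary success rule, a discomfort score of at most 10 means grade 1 on all ten items, and one grade 2 anywhere fails the patient regardless of the other two components. This rests only on the article's own item list, grading and maximum.

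The consequence for the design is that 0.60 and 0.85 are unsupported under the rule as written, so the 80% power is not established and could be lower or higher. The per-item figures rest on assumed probabilities and correlation; they show how demanding the rule is and do not forecast the result. Because the threshold decides the primary analysis, it must be corrected.

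**What to change.** 1. Before any look at data by arm, reconcile the cut-off with the 1–5 grading by placing it above the scale minimum, and state why that value was chosen. For illustration, at most 20 of 50 is a mean grade of at most 2. It is the same rule as at most 10 after rescoring the items 0–4, because each of the ten items drops by 1 (20 − 10 = 10). Its only support in the article would be symmetry with the distention cut (a mean grade of at least 4), so the sponsor must justify the value it adopts.
2. State the ten items and the attainable range next to the cut-off.
3. Re-justify both planning proportions under the final rule, and restate the power at 96 patients.

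Cost: a short amendment and a recalculated power statement. The downside is that the primary definition changes after 29 patients were enrolled, in an open-label trial with discomfort reported by the patients. The date of the change and the absence of any analysis by arm before it must therefore be documented.

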### Statistical analysis plan

Considering the evaluation for grade of bowel distention, we will calculate the mean, standard deviation, and range of distention scores for each bowel segments and total segments between the two groups by using the Wilcoxon rank sum test. Similarly, we will use the same methods to analyze adverse symptom severity and the accuracy of lesion detection between the two groups. We will compare the proportion of bowel preparation for MRE reaching physician–patient satisfaction score between two groups by using the Chi-square test as our primary analysis. We will also explore the correlations between grade of bowel distention and severity of adverse symptoms by using Spearman’s correlation coefficient. The patients’ preference between the two methods for MRE will be compared using the signed-rank test. All statistical analysis will be done using SPSS software (version 19.0; SPSS Inc., Chicago, IL). *P* < 0.05 will be considered statistically significant.

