### Randomization

Randomized sequences will be generated by the statistician from Department of Biostatistics, Nanjing Medical university. SAS 9.4 software will be used to generate a random sequence table for the participants. Ninety-six random numbers and the allocation sequence table of the randomized group will be kept as blind codes. The participants will be randomly divided into the oral group (n = 48) and tubing group (n = 48) at a ratio of 1:1. This sequence of randomization will be contained in opaque sealed envelopes and kept by the clinical research coordinator, who will be contacted competitively by each physician to provide the allocation. The principal physicians from the above three centers are responsible for enrolling patients.

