In our study, we will use a novel and quick technique of enteral tubing under gastroscopy named mid-gut TET [11]. In our previous study, 86 patients underwent mid-gut TET and the success rate of the procedure was 98.8% (85/86) [11]. In addition, 97.7% (84/86) of patients were satisfied with the procedure of placement [11]. This mid-gut tube can serve as the delivery way of FMT, enteral nutrition support, and laxative agents and contrast solution for MRE bowel preparation. The laxative agents and contrast solution infusion rate is about 30 mL/min on average. A pump is not needed in the procedure of bowel preparation for MRE through mid-gut tube. Patients can prepare everything by themselves following the physicians’ instructions. They simply need to hang the bottle or sack for laxative agents and contrast solution on the infusion support and fully open the click for controlling the infusion rate. As observed from the pilot study, patients having difficulty in drinking large volumes of solution benefited from mid-gut tubing, with adverse symptoms alleviated or removed. This result is contrary to Negaad’s study probably because of the infusion rate of contrast solution. The infusion rate in Negaad’s study was 120–150 mL/min [20], which is almost 4–5 times of that in our study.

Above all, we assume that the novel, more acceptable, and more time-saving mid-gut tubing for MRE can lead to better bowel distention and less adverse symptoms, and subsequently higher accuracy of lesion detection to reach physician–patient satisfaction. This study aims to provide evidence to support the assumption. Physician–patient satisfaction emphasizes the fact that physicians and patients are satisfied with the accuracy of lesion detection and the reduction of pain, respectively. The results of this study are expected to provide an important basis for the clinical protocol of bowel preparation for MRE in patients with CD.

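### The exploratory Spearman correlations between distention and symptoms do not account for arm; if computed over all 96 patients they would be biased in the negative direction under the trial's own hypothesis

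*Protocol article*

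**What the plan says.** The Statistical analysis plan section of the protocol article gives this analysis one sentence: the trial will "explore the correlations between grade of bowel distention and severity of adverse symptoms", with Spearman's coefficient as the measure. It mentions neither stratification by arm nor adjustment for arm. The section sets one significance threshold, P < 0.05, and does not exempt this analysis from it. The primary analysis is a different one, a Chi-square test on the proportion of preparations that reach the physician–patient satisfaction score.

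The Discussion states the trial's hypothesis: mid-gut tubing "can lead to better bowel distention and less adverse symptoms". Patients are allocated "at a ratio of 1:1", 48 to each arm.

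**The concern.** Under the stated hypothesis, arm is a common cause of the two variables being correlated: it raises one and lowers the other. A coefficient over all patients therefore mixes two things. One is the association between distention and symptoms among patients prepared by the same method. The other is the difference between the methods, which the between-arm comparisons already estimate. With opposite shifts, the second part is always negative.

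The patient-level question has practical interest: does fuller distention cost the patient more bloating or pain? A coefficient pulled downward could suggest that there is no such cost, or that better distention goes with less discomfort, when it reflects only which arm the patients were in. Calling the analysis exploratory does not tell a reader this.

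**Working it through.** **The plan's own figure.** No figure is given for the correlation. The only design figure is in the Sample size calculation section: "Group sample sizes of 48 in the tubing group and 48 in the oral group achieve 80% power", by a "two-sided Z test with unpooled variance", with the tubing proportion "assumed to be 0.6000 under the null hypothesis and 0.8500 under the alternative hypothesis" and the oral proportion 0.60.

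- SE = √[(0.60 × 0.40 + 0.85 × 0.15)/48] = √(0.3675/48) = 0.0875.
- Power = Φ(0.25/0.0875 − 1.96) = Φ(0.897) = 81.5%; exact binomial enumeration gives 81.6%.

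The stated 80% is reproduced closely enough. It concerns the composite proportion and does not depend on the correlation.

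**Formula for the correlation.** Take two arms of equal size, unit within-arm SD and within-arm correlation r in both arms. Let tubing raise distention by d SD and lower symptoms by d SD. Over all patients, the covariance is r − d²/4 and each variance is 1 + d²/4, so

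all-patient r = (r − d²/4)/(1 + d²/4).

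The values of d and r are assumptions; the document gives neither.

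- d = 0.5, d²/4 = 0.0625. For r = 0: −0.0625/1.0625 = −0.06. For r = +0.3: 0.2375/1.0625 = +0.22. For r = −0.3: −0.3625/1.0625 = −0.34.
- d = 0.8, d²/4 = 0.16. For r = 0: −0.16/1.16 = −0.14. For r = +0.3: 0.14/1.16 = +0.12. For r = −0.3: −0.46/1.16 = −0.40.
- d = 1.0, d²/4 = 0.25. For r = 0: −0.25/1.25 = −0.20. For r = +0.3: 0.05/1.25 = +0.04. For r = −0.3: −0.55/1.25 = −0.44.

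**Check by simulation.** The formula is for Pearson's coefficient on continuous scores, so Spearman's coefficient was simulated on integer totals: distention limited to 5–25, symptoms to 10–50, 48 patients per arm, 1,500 trials per setting. The score means and SDs were assumed and were not calibrated to the satisfaction thresholds.

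| Shift d (SD) | r = 0: mean all-patient rho | r = 0: significantly negative | r = +0.3: mean all-patient rho | r = +0.3: significantly positive | r = −0.3: mean all-patient rho |
|---|---|---|---|---|---|
| 0 | 0.00 | 3% | +0.28 | 80% | −0.28 |
| 0.3 | −0.02 | 4% | +0.25 | 72% | −0.30 |
| 0.5 | −0.05 | 7% | +0.21 | 54% | −0.33 |
| 0.8 | −0.14 | 25% | +0.10 | 16% | −0.38 |
| 1.0 | −0.20 | 49% | +0.02 | 3% | −0.43 |
| 1.5 | −0.37 | 97% | −0.21 | 0% | −0.55 |

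**After the change.** Computed within each arm and averaged, the mean coefficient stays near its no-shift value at every d tried: about 0.00 for r = 0, 0.27 to 0.28 for r = +0.3, and −0.27 to −0.28 for r = −0.3.

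**What shift is plausible?** As a rough scale only, a move from 60% to 85% on a single normal score is z(0.85) − z(0.60) = 0.78 SD. The success criterion has three parts, however. If these were independent and shared the effect equally, each would move from 0.60^(1/3) = 0.843 to 0.85^(1/3) = 0.947, about 0.61 SD. The formula then gives −0.093/1.093 = −0.085 for r = 0. Neither figure is a stated assumption of the trial.

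**The case against.** The strongest reply is that the text does not say the arms are taken together. It is silent, and it speaks of correlations in the plural, which fits coefficients by segment, by symptom or by arm. The neighbouring sentences mention the two groups because they describe comparisons, so the absence of that wording here proves little. A full analysis plan, not shown, may settle the matter. This stands: the article does not prescribe a single all-patient coefficient, and a reader should not infer that it does.

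A second reply is that an all-patient coefficient is a valid description of the marginal association and misleads only if read as a relation within a method. That is true, and the article does not propose such a reading. But the marginal coefficient adds little to the arm comparisons, and the patient-level reading is the natural one.

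A third reply is that the effect may be small. This also stands. The Discussion gives a direction for both variables and no magnitude, and it cites one study of 21 patients that found no significant difference in distention between the methods. At 0.5 SD or less, the spurious negative is slight and a true +0.3 is weakened but still visible. If tubing moved only one of the two variables, the arm term in the covariance would vanish and no spurious correlation would arise.

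What survives is that the sentence, followed literally, includes no step that removes the arm effect, while the trial's own hypothesis predicts one in opposite directions.

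**Conclusion.** This is a minor point that costs nothing to put right. If the correlations are computed over all 96 patients, and if tubing raises distention and lowers symptoms as the Discussion expects, the coefficient is biased in the negative direction. With equal and opposite shifts, the bias is small up to 0.5 SD and becomes material from about 0.8 SD in both variables.

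A reader might infer that the trial's hypothesis makes a spurious negative correlation, or the concealment of a real positive one, a certainty. The document does not support that. It gives no shift sizes, a positive association may only be weakened, and a real negative one would be exaggerated. The 49% chance of a spurious significant negative belongs to an assumed 1 SD shift in both variables and should not be quoted as the expected result.

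The primary Chi-square test, the sample size and the between-arm Wilcoxon comparisons do not depend on this analysis.

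**What to change.** Add one sentence to the Statistical analysis plan section. Spearman's coefficient between distention and symptom severity will be computed within each arm and the two values combined by averaging on Fisher's z scale; alternatively, a partial rank correlation adjusted for arm will be used. Report the arm-specific values alongside, and do not interpret an all-patient coefficient as the patient-level association.

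This needs no extra data and about one line of code. The loss of precision is negligible: on Fisher's z scale the information is proportional to n − 3, which is 45 + 45 = 90 for two arms of 48, against 93 for 96 patients taken together.

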## Methods/design

This study is conducted in China as an open-label, multicenter RCT with a parallel group design. Flow chart of the trial is shown in Fig. 1. The procedure and checklist of this trial are shown in SPIRIT figure (Fig. 2) and Additional file 1: SPIRIT checklist, respectively.

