### Oral group

Patients will be instructed to drink 2000 mL polyethylene glycol (PEG) solution over 60 min on the night before the MRE to remove stool and other impurities which may mimic lesions in the MRE. In addition, they will drink 1500 mL 3% mannitol solution gradually in the course of 60 min before MRE. An example of bowel preparation for MRE through oral administering is shown in Fig. 3a. If a patient fails to complete bowel preparation because of severe adverse symptoms such as nausea, vomiting, bloating, and abdominal pain and/or refusing to choose “oral” method, a tube will be placed in his or her mid-gut for MRE. Patients in the oral group will have a soft tube placed in the mid-gut after MRE for enteral nutrition or FMT.

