### Procedures

Over the one-week study period, the included patients will be instructed to answer a questionnaire about their mental pressure and discomfort (such as nausea, vomiting, bloating, abdominal pain, and diarrhea) before/during/after the bowel preparation for MRE. An overview of corresponding assessments is showed in Table 1. Two experienced radiologists will evaluate the grade of bowel distention. Two experienced endoscopists will evaluate the colonoscopy results.

**Table 1 Tab1:** Summary of measures to be collected

Variable				
Visit number/bowel preparation	0/Screening	1/Before	2/During	3/After
Day	~ − 3	− 1	0	1~3
Female-sex (%)	A	–	–	–
Age (years) (mean ± SD)	A	–	–	–
Height (mean ± SD)	A	–	–	–
Weight (mean ± SD)	A	–	–	–
Disease duration (years) (mean ± SD)	A	–	–	–
Disease location (n)	A	–	–	–
Small bowel disease	A	–	–	–
Small bowel + colonic disease	A	–	–	–
Upper GI	A	–	–	–
Perianal disease	A	–	–	–
Previous CD-related surgery (n)	A	–	–	–
HBI	A	–	–	–
Current medication (n)	A	–	–	–
Systematic corticosteroids	A	–	–	–
Thiopurines	A	–	–	–
Mesalazine	A	–	–	–
Anti-TNF	A	–	–	–
Mental pressure (median)	–	A	–	–
Degree of discomfort (median)	–			
Nausea	–	A	A	–
Vomiting	–	A	A	–
Bloating	–	A	A	
Abdominal pain	–	A	A	A
Diarrhea	–	–	–	A
Distention grade (median)				
Jejunum	–	–	A	–
Ileum, proximal	–	–	A	–
Ileum, distal	–	–	A	–
Colon (right part)	–	–	A	–
Colon (left part)	–	–	A	–
Preference to the method (n)	–	–	–	A
MRE lesion detection	–			
Terminal ileum	–	–	–	A
Ileocecal junction	–	–	–	A
Hepatic flexure of colon	–	–	–	A
Splenic flexure of colon	–	–	–	A
Rectosigmoid colon	–	–	–	A

*A* assessed, − not assessed, *SD* standard deviation, *GI* gastrointestinal, *CD* Crohn’s disease, *HBI* Harvey Bradshaw Index, *TNF* tumor necrosis factor

Mental pressure and degree of discomfort: using a visual 5-grade to describe (1 = few, 5 = very severe); distention grade of bowel segments: using a 5-grade scale (1 = 0–20% segmental distention, 2 = 20–40% distention, 3 = 40–60% distention, 4 = 60–80% distention, 5 = 80–100% distention); ileum, distal (the last 20–25 cm of terminal ileum). MRE lesion detection is evaluated by a 5-point scale (lesions locating at the terminal ileum, ileocecal junction, hepatic flexure of colon, splenic flexure of colon, and rectosigmoid colon, consistency of lesion detection from each bowel segment scoring 1 point, otherwise not scoring, confirmed by colonoscopy)

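### The signed-rank test planned for patient preference needs paired, ordered scores; on the single count that Table 1 describes it becomes a pooled sign test that ignores the randomised arm

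*Protocol article*

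**What the plan says.** The Statistical analysis plan section of the Protocol article states that patients' "preference between the two methods for MRE will be compared using the signed-rank test". For distention, symptom severity and lesion-detection accuracy, the same section compares the groups "by using the Wilcoxon rank sum test", an unpaired test. For the proportion reaching the satisfaction score it uses a chi-square test.

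Methods/design describes an "open-label, multicenter RCT with a parallel group design". Under Randomization, patients are allocated "at a ratio of 1:1", 48 to each arm, and each arm is assigned one preparation method.

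Table 1 (Procedures) carries preference in a single row beginning "Preference to the method (n", assessed only at the visit after preparation. Scored items in the same table are labelled differently, for example "Mental pressure (median". The table's footnote defines scales for mental pressure, discomfort, distention and lesion detection, but none for preference.

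**The concern.** A signed-rank test takes two measurements per patient, or one signed difference, and uses both the sign and the size of that difference. The article describes neither for preference. Patients are assigned to one method, and the oral arm has no planned second preparation to rate: "Patients in the oral group will have a soft tube placed in the mid-gut after MRE", and that tube is for enteral nutrition or FMT.

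If the named test is run on one choice per patient, the software will still return a p value. A reader of a randomised trial would probably take it as a comparison of the arms, which it would not be. It could hide a large difference between the arms, or be highly significant when the arms agree completely.

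**Working it through.** **Inputs.** From the Protocol article: 48 patients per arm, 96 in all (Randomization); one preference per patient, recorded as a count (Table 1, inferred from the label). Assumed for illustration: the numbers preferring tubing in each arm, since the article gives no expected preference figure.

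**The plan's own figure.** There is none for preference. The stated sample size, said to "achieve 80% power to detect a difference between the group proportions of 0.2500", was reproduced only to confirm the arm size. With proportions 0.85 and 0.60 and unpooled variance, SE = √[(0.85×0.15 + 0.60×0.40)/48] = √(0.3675/48) = 0.0875. Power = Φ(0.25/0.0875 − 1.96) = Φ(0.897) = 0.815, in line with the stated 80%.

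**What the signed-rank test becomes.** Code a choice of tubing as +1 and of oral as −1. All 96 absolute values equal 1, so each gets the mid-rank (96 + 1)/2 = 48.5. With k patients preferring tubing:

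- sum of positive ranks = 48.5k
- null mean = 48.5 × 96/2 = 48.5 × 48
- null standard deviation = 48.5 × √96/2
- z = 48.5(k − 48) / (48.5√96/2) = (2k − 96)/√96

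The ranks cancel. What remains is the sign test of a 50:50 split. It depends only on the total k, and treatment arm does not enter.

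**Numerical check.** The between-arm column is the chi-square test without continuity correction on the 2×2 table.

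| Prefer tubing: tubing arm | Prefer tubing: oral arm | k | z | Signed-rank p | Between-arm chi-square p |
|---|---|---|---|---|---|
| 40/48 | 8/48 | 48 | 0 | 1.00 | 6.5e-11 |
| 40/48 | 40/48 | 80 | 64/9.80 = 6.53 | 6.5e-11 | 1.00 |
| 40/48 | 30/48 | 70 | 44/9.80 = 4.49 | 7.1e-6 | 0.022 |
| 29/48 | 29/48 | 58 | 20/9.80 = 2.04 | 0.041 | 1.00 |

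In the first row the arms differ by 32/48, or 67 percentage points, and the planned test sees nothing. In the second row the arms are identical and it is overwhelmingly significant. In the last row the exact binomial test gives p = 0.052 where the signed-rank approximation gives 0.041, so even for a pooled question the choice of test can matter at the 0.05 threshold.

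**Precision of a between-arm comparison.** With both proportions at 50%, the 95% half-width for the difference is 1.96 × √(0.25/48 + 0.25/48) = 1.96 × 0.102 = 0.200, about ±20 points. This is the precision of the replacement analysis; it does not measure how wrong the planned p value would be.

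**The case against.** The strongest reply is that the sentence speaks of the two methods, whereas the other comparisons in that section are described as between the two groups. The authors may therefore mean a one-sample question: do more patients prefer tubing or oral preparation? For that question the collapsed test is a legitimate sign test, apart from the choice of approximation. This stands, and it rules out calling the p value invalid outright. It does not rescue the wording: there would still be no magnitudes to rank, the proper name would be a binomial or sign test, and the result would not be a randomised comparison.

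Second, the single-choice format is inferred from the count label, the single visit and the absence of a defined scale. The questionnaire is not reproduced. This also stands, but nothing in the article describes a paired or graded preference.

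Third, a reader might infer that every patient knows only the assigned method. The article does not support this. The Oral group section provides for a tube before MRE when oral preparation fails or is refused. The Tubing group section offers an alternative when the tube is refused, falls off or blocks. Some oral-arm patients may also have had their later tube placed before they answer. These exceptions qualify how the result is described. They do not create pairing, because the patients who switch are a non-random subset.

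**Conclusion.** The named test does not fit the data that the article describes. On one choice per patient it tests a pooled 50:50 split and carries no information about the difference between the randomised arms; the assumed counts show it can mislead in either direction. This rests on preference being a single nominal choice, which is the natural reading of Table 1 but is not written out.

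The reach is limited. Preference is not among the primary or secondary outcomes and does not enter the satisfaction score or the sample size. A reader might infer that the trial's main conclusion is at risk; it is not. The point should be corrected, but it is minor.

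**What to change.** Replace the sentence on preference. Compare the proportion preferring tubing between the arms as randomised, using a chi-square or Fisher exact test chosen in advance, and report the difference with its 95% confidence interval.

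If the pooled question is also of interest, name it a one-sample binomial (sign) test and present it as descriptive, not as a randomised comparison. Note beside it that most patients will have used only their assigned method, apart from those who switched under the provisions in the Oral group and Tubing group sections.

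State the response options of the preference question, so that the match between data and test can be seen.

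The cost is one or two sentences. If the recorded item is the choice between the two methods, the data already planned suffice. The preference question should stay as it is: asking instead whether patients would choose their own method again is a different item and could need new data, with 29 patients already included according to Trial status.
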